### Recruitment

Promotional seminars and booths will be conducted in the facilities for older adults (e.g. community centres for older adults, residential care homes for older adults) and tertiary institutions. In the seminars, participants will be directly recruited. The programme will be introduced to collaborative organizations. Both printed and electronic posters will be produced and sent to the members of the collaborative organizations. The staff members of the collaborative organizations will help recruit their members to participate in this project. The estimated rate of recruitment is 90% because most of the participants could fulfil the eligibility criteria and they self-enrol to participate after reading the information that they are highly likely to give consent to participate in the study.

### Assignment of interventions

As shown in Fig. 2, the cluster randomization method was employed to reduce the risk of within-cluster contamination because most of the training materials are open source that participants share with their peers in a cluster [45]. A permuted block (block size = 6) random allocation sequence list with an allocation ratio to either intervention group or control at 1:1 will be generated by the web-based application www.random.org. The cluster unit of randomization is based on a facility for older adults (e.g. one community centre as a unit). Each unit will be randomly assigned after the entire unit is screened, written consent is obtained, and baseline assessment is completed to reduce the risk of selection bias [46]. A group of six units (i.e. the size of a permuted block) with a similar number of eligible and consented participants will be grouped to be randomly allocated. This aims to ensure each group comprises a similar number of participants. The random allocation process will be implemented by an independent statistician, who will not participate in any other parts of the proposed study. The statistician will assign group labels to each unit based on their sequence of entries with reference to the sequence list, thus ensuring that other members of the research team cannot foresee the group allocations. In this study, only the outcome assessor will be blinded to the group labels. It will not be possible to blind the participants or the interventionists. In the intervention group, we will conduct interventions for the three clusters simultaneously when we have secured the study venues and done the randomization.

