### Study setting

The study will be conducted in facilities for older adults, including community centres and/or long-term care facilities for older adults in Hong Kong. Community centres for older adults provide various activities aiming to enable older adults to remain in the community and to lead a healthy, respectful, and dignified life [30]. Long-term care facilities for older adults provide residential care, meals, personal care, and nursing care for older adults who suffer from poor health or physical/mild mental disability [31].

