### Statistical methods

Demographic and outcome data at baseline will be described either as means with standard deviation or as frequencies with percentages based on the level of measurement. Five generalized estimating equations (GEE) will be used to separately test the five outcomes. To test the hypotheses, the dependent variables will be mental well-being, depressive symptoms, health-related quality of life, self-efficacy, and social support across the two time points. The independent variables of the four hypotheses will be the same: group (i.e. intervention and control groups), time (i.e. T0 and T1), and group × time. The interpretation of the results will be based on intention-to-treat analysis [47]. We will primarily interpret the results using models without adjusting for possible co-variates because this will be an RCT without other known or anticipated important prognostic variables [48]. The level of significance will be set at 0.05. To manage missing data caused by unavoidable reasons (e.g. drop-out), the missing data will be replaced by multiple imputations following Jakobsen’s algorithm [49]. We will adopt an intention-to-treat analysis to conclude the intervention effects [47].

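### If the six facilities mix community centres and long-term care homes, facility type is neither balanced by the randomisation nor in the primary model, and the reason given for not adjusting is poorly supported

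*Protocol article*

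**What the plan says.** Study setting admits facilities "including community centres and/or long-term care facilities for older adults in Hong Kong", and Recruitment names both types as venues, so a mixed sample is allowed. Study setting also separates the two types. Centres run activities that help older people stay in the community. Homes provide residential, personal and "nursing care for older adults who suffer from poor health or physical/mild mental disability".

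Assignment of interventions fixes the unit and the scheme: "The cluster unit of randomization is based on a facility for older adults", allocated 1:1 from "A permuted block (block size = 6) random allocation sequence list". The six units to be randomised together are chosen for similar numbers of participants: "A group of six units (i.e. the size of a permuted block) with a similar number of eligible and consented participants will be grouped". The purpose given is numerical: "This aims to ensure each group comprises a similar number of participants". Facility type is not mentioned. Sample size gives six clusters in total, and Assignment of interventions refers to three in the intervention group.

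In Statistical methods, the GEE for each outcome contains group, time and their interaction. Interpretation rests primarily on models without covariates, on the ground that "this will be an RCT without other known or anticipated important prognostic variables".

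**The concern.** When many individuals are randomised, leaving out a prognostic factor usually does little harm, because chance imbalance is small. Three facilities against three is a different situation: a facility-level factor takes at most four values per arm (0, 1, 2 or 3 homes), and large gaps are common.

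Facility type plausibly matters here. By the protocol's own account the homes serve people in poorer health, and the Introduction links mental well-being to health-related quality of life, social support and self-efficacy. The comparator is usual care, which in a home means residential and nursing care and in a centre means activities. An uneven split would therefore alter the control condition as well as the case mix.

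At stake is how the treatment contrast can be read. If residents and community dwellers change differently over six months, or respond differently to the programme, an uneven split would put part of that difference into the estimated effect. The primary model has no term to separate the two.

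**Working it through.** **Inputs from the protocol.** Six facilities, three per arm (Sample size; Assignment of interventions); planning effect d = 0.5 (Sample size); model terms group, time and group × time (Statistical methods). The protocol gives no figure for imbalance by setting, so there is none to reproduce.

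**Inputs that are assumptions.** The number of homes among the six, L, is not stated, so every mix from 1 to 5 is shown. Facilities are taken as equal in size, which is the protocol's own aim. The difference between settings in mean six-month change, D, is not stated; 0.2 to 0.5 SD is shown.

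**Step 1: chance of imbalance.** There are C(6,3) = 20 equally likely allocations. The probability that x homes fall in the intervention arm is C(L,x) × C(6−L, 3−x) / 20. The gap between arms in care-home share is |2x − L| / 3.

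- L = 2: x = 1 arises in C(2,1) × C(4,2) = 12 allocations (gap 0). x = 0 or 2 arises in 4 + 4 = 8 (gap 2/3).
- L = 3: x = 1 or 2 arises in 9 + 9 = 18 allocations (gap 1/3). x = 0 or 3 arises in 1 + 1 = 2 (gap 1).
- L = 1: x = 0 or 1 arises in 10 + 10 = 20 allocations (gap 1/3).
- L = 4 and L = 5 mirror L = 2 and L = 1.

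| Homes among six | No gap | 33 points | 67 points | 100 points |
|---|---|---|---|---|
| 1 or 5 | 0 | 100% | 0 | 0 |
| 2 or 4 | 60% | 0 | 40% | 0 |
| 3 | 0 | 90% | 0 | 10% |
| 0 or 6 | 100% | 0 | 0 | 0 |

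**Step 2: what reaches the planned estimator.** The group × time term estimates (T1 − T0 in intervention) − (T1 − T0 in control). A setting difference of the same size at T0 and T1 adds gap × difference at each time and cancels. A difference D in mean change does not cancel; it shifts the contrast by gap × D.

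| D (assumed) | 33 points | 67 points | 100 points |
|---|---|---|---|
| 0.2 SD | 0.07 | 0.13 | 0.20 |
| 0.5 SD | 0.17 | 0.33 | 0.50 |

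Relative to the planning effect, a 67-point gap amounts to 0.13/0.5 = 27% up to 0.33/0.5 = 67%.

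**Step 3: balancing compared with adjusting.** Take 122 per arm, three clusters per arm, ICC 0.01, d = 0.5 and two-sided 0.05. Cluster size is 122/3 = 40.7, the design effect is 1 + 39.7 × 0.01 = 1.40, and SE = √(2 × 1.40/122) = 0.151. Power from a noncentral t distribution is 0.70 on 4 between-cluster degrees of freedom (critical value 2.78). It is 0.61 on 3 (critical value 3.18), the position if a facility-type term takes one degree of freedom and explains nothing. This is an illustration on cluster-level degrees of freedom, not the protocol's own power calculation.

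**The case against.** Several points on the other side stand.

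- **The problem is conditional.** The wording on settings permits all six units to be of one type, and the example given for a unit is a community centre. The actual mix is unknown.
- **Chance imbalance is not systematic bias.** Averaged over the 20 allocations the expected shift is zero. The issue is how far a single realised allocation of six units can be trusted.
- **The prognostic role of setting is inferred.** Study setting describes whom each facility type serves, not who is enrolled. Eligibility requires mental capacity and the ability to read Chinese, and participants self-enrol, so enrolled residents may differ less from centre members. Nothing in the document says that facility type predicts change in WHO-5.

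A reader might also infer stronger claims that the document does not support.

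- **That adjustment is ruled out, or that the authors deny any prognostic variable.** Unadjusted models are only the primary basis for interpretation. Secondary adjusted models are not excluded, though none is named. The rationale is limited to further important variables that are known or expected.
- **That a level difference between settings biases the result.** Assuming 0.3 SD on WHO-5, a 67-point gap would shift a raw post-treatment comparison by (2/3) × 0.3 = 0.2 SD. The planned contrast is a difference in change, from which a stable difference drops out.
- **That mixing settings doubles the assumed ICC.** The same 0.3 SD with two homes gives a between-setting variance of (1/3)(2/3)(0.3²) = 0.02, against an ICC of 0.01. This concerns WHO-5 levels, not change, so it does not show that the planned contrast is less precise.
- **That complete confounding is likely.** It needs exactly three homes, and then has a 10% chance.

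**Conclusion.** The point holds in conditional form. If the six facilities are of both types, some imbalance in setting is likely: 40% with 2 or 4 homes, and certain with 1, 3 or 5. Neither the stated randomisation nor the primary model deals with it. The reason given for not adjusting is poorly supported by the protocol's own description of the two settings, although it is not refuted by any figure in the document.

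The consequence is confined to differences in six-month change or response by setting. Its size, 0.13 to 0.33 SD for a 67-point gap, rests wholly on the assumed 0.2 to 0.5 SD difference in change and on facilities of equal size. With all six units of one type there is no problem. This is an inexpensive improvement to the design, and it does not show that the planned analysis is invalid.

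**What to change.** If both facility types are recruited, draw the allocation from a list restricted to those that balance facility type as closely as the mix permits:

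- 2 or 4 homes: 12 of the 20 allocations balance exactly, and the 40% chance of a 67-point gap falls to zero.
- 3 homes: 18 of 20 avoid complete confounding, but a 33-point gap remains.
- 1 or 5 homes: a 33-point gap cannot be avoided, and the report should say so.

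In Statistical methods, delete or correct the statement that no further important prognostic variables are expected.

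The change is practicable. Units are randomised only after screening, consent and baseline assessment, so facility type is known in time, and the independent statistician needs only a shorter list. The cost is fewer admissible allocations, and fewer still if size is restricted as well. Balancing in the design is preferable to relying on a covariate alone, which would use one of about four between-cluster degrees of freedom. Limiting the trial to one setting would also remove the problem, but it trades away generalisability and is not needed.

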**Fig. 2 Fig2:**
[figure not shown]
Cluster randomization method

A waitlist control design will be adopted so that the participants randomized into the control group will be provided with a chance to receive the intervention after they have completed their untreated condition (i.e. receiving usual care for 6 months).

### Statistical methods

Demographic and outcome data at baseline will be described either as means with standard deviation or as frequencies with percentages based on the level of measurement. Five generalized estimating equations (GEE) will be used to separately test the five outcomes. To test the hypotheses, the dependent variables will be mental well-being, depressive symptoms, health-related quality of life, self-efficacy, and social support across the two time points. The independent variables of the four hypotheses will be the same: group (i.e. intervention and control groups), time (i.e. T0 and T1), and group × time. The interpretation of the results will be based on intention-to-treat analysis [47]. We will primarily interpret the results using models without adjusting for possible co-variates because this will be an RCT without other known or anticipated important prognostic variables [48]. The level of significance will be set at 0.05. To manage missing data caused by unavoidable reasons (e.g. drop-out), the missing data will be replaced by multiple imputations following Jakobsen’s algorithm [49]. We will adopt an intention-to-treat analysis to conclude the intervention effects [47].

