### Outcomes

Demographic data will be collected at baseline (T0), including age, gender, education attainment, employment status, financial satisfaction, living arrangement, years of smartphone usage, daily average of internet usage, perceived ability to use a smartphone, and perceived ability to use the internet. Five outcome markers will be measured at both baseline (T0) and the week immediately after the completion of the intervention (T1). The primary outcome is mental well-being. Four secondary outcomes will also be measured, including depressive symptoms, health-related quality of life, self-efficacy, and social support.

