### Sample size

We adopt a prior power analysis using the GPower employing the statistical test of the mean difference between two different groups. We set the level of significance at 0.05, the power at 0.8, and the allocation ratio between the two groups at 1:1. To estimate the effects, we refer to a similar pilot trial examining the effect of an intergenerational mentoring programme [43]. The effect size (i.e. Cohen’s *d*) of the study of the intervention on the primary outcome (i.e. well-being) was 0.5. A sample size of 102 participants is needed. We adopt Hemming’s method to adjust the sample size required under individual randomization for cluster RCT with fixed and equal-sized number clusters [44]. Considering that we will collect data in 6 clusters and assuming that the intra-cluster correlation coefficient (ICC) is 0.01, the estimated total sample size is 244 (i.e. 122 per arm). We assume that the drop-out rate is approximately 20%. A total sample of 292 is estimated, with 146 participants in each arm.

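### The primary contrast is an unadjusted difference in mean change, which fixes the weight on baseline WHO-5 at 1; conditioning on baseline would usually be more precise at almost no cost

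*Protocol article*

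**What the plan says.** The Outcomes section states: "Five outcome markers will be measured at both baseline (T0) and the week immediately after the completion of the intervention (T1"). Under Statistical methods the dependent variables are "mental well-being, depressive symptoms, health-related quality of life, self-efficacy, and social support across the two time points", and the model terms are "group (i.e. intervention and control groups), time (i.e. T0 and T1), and group × time". The T0 score therefore enters as an outcome row and not as a covariate. On adjustment the same section says: "We will primarily interpret the results using models without adjusting for possible co-variates because this will be an RCT without other known", and the sentence continues to include anticipated prognostic variables of importance.

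On allocation, the Assignment of interventions section says: "Each unit will be randomly assigned after the entire unit is screened, written consent is obtained, and baseline assessment is completed". Units of similar size are grouped into one block of six, and of that grouping it says: "This aims to ensure each group comprises a similar number of participants". No other balancing factor is named. The Sample size section gives the number of units and the ICC: "Considering that we will collect data in 6 clusters and assuming that the intra-cluster correlation coefficient (ICC) is 0.01". Three units fall in the intervention arm ("we will conduct interventions for the three clusters simultaneously").

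**The concern.** A difference in change scores subtracts the whole of the baseline value. When T0 and T1 are imperfectly correlated, that is more than the data support. It adds noise, and it over-corrects a transient chance difference at baseline through regression to the mean.

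The reason given for leaving the model unadjusted is the absence of other important prognostic variables in a randomised trial. That does not meet the point. The baseline value of the outcome is likely to be prognostic, and randomising six facilities does not ensure that the arms are alike on it. The Study setting section also allows community centres, long-term care facilities or both. The Introduction links social support and self-efficacy to mental well-being, and both are measured at T0.

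At stake is precision, and the sensitivity of the headline estimate to baseline imbalance, in a design with very few randomised units.

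**Working it through.** **Inputs from the protocol article.** Six facilities, three per arm; ICC 0.01; target effect d = 0.5; cluster-adjusted total 244, so 244/6 ≈ 41 per facility. **Assumed, because not given:** the T0–T1 correlation r (0.3 to 0.7), equal SDs at T0 and T1, an alternative ICC of 0.05, and the correlation of facility effects between T0 and T1 (0.5 or 0.8).

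**The plan's own figure.** The protocol gives no precision figure for this model. Its individually randomised total of 102 is reproduced by a one-sided two-sample t-test (51 per arm); a two-sided test gives 128. Either way the basis is a plain two-group mean difference that does not use r.

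**Step 1: what the model estimates.** The stated GEE was fitted to a simulated complete data set of six facilities of 41. The group × time coefficient was 0.5888 and the difference in mean change was 0.5888. They agreed under independence and exchangeable working correlation, with person or facility as the cluster.

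**Step 2: individual-level efficiency.** In units of the outcome variance, the change score has variance 2(1 − r) and ANCOVA has 1 − r². The ratio is 2(1 − r)/(1 − r²) = 2/(1 + r):
- r = 0.3: 1.40/0.91 = 1.54
- r = 0.5: 1.00/0.75 = 1.33
- r = 0.7: 0.60/0.51 = 1.18

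**Step 3: chance imbalance at T0.** With 3 × 41 = 123 per arm, the SD of the baseline difference is √(2 × [1 + 40 × ICC]/123).
- ICC 0.01: √(2 × 1.4/123) = 0.15 SD, 95% range ±0.30
- ICC 0.05: √(2 × 3.0/123) = 0.22 SD, 95% range ±0.43

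For individual-level imbalance the change score is shifted by about −(1 − r) times the imbalance. At r = 0.5 and an imbalance of 0.30 SD the shift is 0.5 × 0.30 = 0.15 SD, against a target of 0.5.

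**Step 4: simulation of three against three facilities of 41, true effect 0.50.** The four values in each cell are for r = 0.4, 0.5, 0.6 and 0.7. The last two columns average the draws in which the intervention arm's baseline mean was more than 0.2 SD higher.

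| ICC | Facility-effect correlation | Variance ratio, change/ANCOVA | Change estimate, imbalanced draws | ANCOVA estimate, imbalanced draws |
|---|---|---|---|---|
| 0.01 | 0.5 | 1.37, 1.31, 1.30, 1.20 | 0.340, 0.365, 0.391, 0.413 | 0.504, 0.498, 0.500, 0.496 |
| 0.01 | 0.8 | 1.27, 1.23, 1.18, 1.15 | 0.373, 0.384, 0.403, 0.421 | 0.534, 0.521, 0.512, 0.502 |
| 0.05 | 0.5 | 1.34, 1.34, 1.30, 1.25 | 0.330, 0.339, 0.343, 0.355 | 0.524, 0.499, 0.471, 0.450 |
| 0.05 | 0.8 | 1.06, 1.07, 1.08, 1.09 | 0.405, 0.416, 0.414, 0.429 | 0.593, 0.576, 0.542, 0.527 |

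At ICC 0.01 the ratio is 1.15–1.37. At ICC 0.05 with strongly stable facility effects it falls to 1.06–1.09.

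**The case against.** Several points on the other side stand.

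- **Baseline is used.** A reader might infer that the T0 measurement is wasted. It is not: it is in the model as the T0 outcome. When r exceeds 0.5 the change contrast is already more precise than T1 alone. Individually randomised totals for d = 0.5, two-sided, 80% power (change, ANCOVA, T1 only) are 176, 116, 126 at r = 0.3; 126, 96, 126 at r = 0.5; and 76, 66, 126 at r = 0.7. So, against a T1 comparison of the kind used for sizing, the planned contrast falls short only when r is below 0.5.
- **The rationale says other variables.** A reader might take the sentence to deny that T0 is prognostic. It can be read as meaning variables beyond those already modelled, and on that reading it is not contradicted by T0. It still gives no reason for a weight of 1.
- **The analysis is valid.** A reader might infer bias. The shift in steps 3 and 4 is conditional on an observed imbalance; over randomisations the estimator is unbiased. The protocol's wording also leaves room for adjusted secondary models.
- **The ratio 2/(1 + r) is an individual-level figure.** At r = 0.5 it is tempting to say that the plan needs one third more participants. With six fixed facilities, a variance ratio does not convert one-for-one into participants, and the clustered ratio can be much smaller.
- **ANCOVA is not a complete cure.** If facility differences are stable, a weight of 1 is closer to right and individual-level adjustment under-corrects (0.527–0.593 in the last row of the table). In that same row the change score errs the other way by at least as much (0.405–0.429).

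These points limit the size of the concern. None is a reason to prefer the unadjusted change contrast as the primary result.

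**Conclusion.** The point holds as a matter of efficiency and justification. The headline effect is an unadjusted difference in mean change, and the stated rationale does not support that choice where a likely prognostic T0 score is measured before allocation and six facilities are balanced only on size.

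The avoidable excess variance is about 15–37% at the protocol's ICC of 0.01, for r between 0.4 and 0.7. It is 25–34% at ICC 0.05 with weakly stable facility effects, and 6–9% at ICC 0.05 with strongly stable ones. All of these rest on assumed r, assumed facility stability and equal facility sizes; the ICC of 0.01 is itself only the protocol's assumption. The documents do not support calling the analysis biased or invalid.

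**What to change.** Make the primary contrast the group difference in T1 WHO-5 adjusted for individual T0 WHO-5, in the facility-clustered model with a small-sample correction for six clusters. An acceptable alternative is a longitudinal model with the group means constrained equal at T0. That version needs a working covariance that represents the within-person correlation; under working independence it reduces to a comparison of T1 alone.

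Do the same for each secondary score, keep the unadjusted group × time result as a sensitivity analysis, and reword the rationale sentence.

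The cost is analysis wording only, best settled before T1 data are examined by group. T0 is already measured before allocation, no participants are added, and an individual-level covariate uses none of the facility degrees of freedom. The small downside is that, if facility effects are stable and the ICC is higher than assumed, the adjustment under-corrects facility imbalance somewhat and the precision gain is small; the sensitivity analysis would help to show this.
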